## 1.4 Treatment planning

IMRT or VMAT may be planned using fixed fields or arcs. The treatment plan to be used for each participant is based on an analysis of volumetric doses including the dose volume histogram (DVH) of the PTV and the OARs. Treatment planning should conform to ICRU 50, 62 and 83 rules for coverage of GTV, CTV and PTV. Additionally, organs at risk (OAR) detailed in Appendix chapter 1.3.4 should be delineated according to the ICRU 62 rules.

OAR planning risk volumes (PRV) should be defined by applying a margin equal to the PTV margin.

### 1.5 Prescribed dose and fractionation

The dose prescribed to the PTV in the experimental arm is 4 fractions of 5.5 Gy. The prescribed dose to the PTVboost is 4 fractions of 7.5 Gy. All fractions should be given within 2 weeks. The maximum dose in the PTVboost of the experimental arm should not exceed 130% of the prescription dose. Maximum dose in the PTV should not exceed 107% of the prescription dose according to ICRU rapport 50. The dose calculation grid should be 3 mm or less.

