## 5. TREATMENT OF SUBJECTS

### 5.1 Treatment Protocol

Radiotherapy will be planned and delivered in every center according to the treatment protocol (Appendix 1).

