## Appendix

### 1. Radiotherapy Treatment Protocol for arm 1

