##### 1.3.1 Gross Tumour Volume (GTV)

The GTV is defined as the contrast enhancing lesion on CE-T1 MRI sequence for both treatment groups. GTV can be expanded using the other clinically acquired MRI sequences according to the expertise of the local radiation oncologist and the medical team.

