##### 1.3.2 Clinical Target Volume (CTV)

The CTV of both, the experimental arm and the standard arm, is defined as the GTV with addition of a 3-dimensional margin of 5 mm limited by anatomic borders. The stereotactic CTVboost of the experimental arm is equivalent to the GTV. CTV can be expanded using the other clinically acquired MRI sequences according to the expertise of the local radiation oncologist and the medical team.

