## 1.8 Treatment Protocol Overview Table

Table A2. Overview of target volume definitions, dose prescription and accepted dose heterogeneity.

\*Depending on radiotherapy center

|                                                               |                                                                          |
|---------------------------------------------------------------|--------------------------------------------------------------------------|
|                                                               | Experimental arm
4 x 5.5 Gy
with 7.5 Gy boost |
| GTV                                                    | Contrast enhancement on T1 MRI                                           |
|                                                               |                                                                          |
| CTV30Gy (boost)                             | GTV                                                                      |
| CTV22Gy                                     | GTV + 5 mm                                                               |
|                                                               |                                                                          |
| PTV30Gy (boost)                             | CTV 30Gy (boost) + 2 or 3 mm                                  |
| PTV22Gy                                     | CTV 22Gy + 2 or 3 mm                                          |
|                                                               |                                                                          |
| Accepted dose heterogeneity PTV30Gy (boost) | 95% - 107%

D max 0.1cc                                 |
| Accepted dose heterogeneity PTV22Gy         | 95% - 130% (exclude PTV 36Gy )

D max 0.1cc  |

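### Appendix 1.5 and Table A2 attach the 107% and 130% maximum-dose limits to opposite target volumes, so the boost maximum is 39.0 Gy in one place and 32.1 Gy in the other

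*Protocol*

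**What the plan says.** Protocol section 5.1 makes Appendix 1 the operative treatment document: "Radiotherapy will be planned and delivered in every center according to the treatment protocol (Appendix 1"). The Appendix then gives maximum doses twice.

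- **Appendix 1.5.** The prescriptions are 4 x 5.5 Gy to the PTV and 4 x 7.5 Gy to the boost PTV. The boost maximum "of the experimental arm should not exceed 130% of the prescription dose". For the outer volume: "Maximum dose in the PTV should not exceed 107% of the prescription dose". This second sentence names no arm and does not exclude the boost.
- **Table A2 (Appendix 1.8).** The row for PTV30Gy (boost) accepts 95% to 107%. The row for PTV22Gy reads "95% - 130% (exclude PTV", and the excluded volume carries the subscript 36Gy. Both rows refer to Dmax 0.1cc.

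Appendix 1.4 asks for conformity with ICRU reports 50, 62 and 83. Neither it nor any other section says whether Appendix 1.5 or Table A2 prevails.

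**The concern.** A hot-spot limit for re-irradiated brain should have one value. Here the 107% and 130% limits sit on opposite volumes, so a planner who reads Appendix 1.5 and a planner who reads Table A2 work to different boost maxima.

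Three things are at stake.

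- **Safety.** These are previously irradiated patients, and section 7.4 provides for no DSMB.
- **Uniformity of the experimental treatment.** Toxicity is a secondary endpoint, and under section 8.3 it drives the restriction on tumour size.
- **Judging compliance.** Section 8.1.1 plans a per-protocol OS analysis that depends on the absence of major protocol violations. A boost maximum of 120% meets the boost limit in Appendix 1.5 and breaches the one in Table A2, so compliance with this limit cannot be judged consistently.

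**Working it through.** **Inputs.** Boost prescription 4 x 7.5 = 30 Gy and outer PTV prescription 4 x 5.5 = 22 Gy (Appendix 1.5). Limits of 107%, 130% and 95% (Appendix 1.5, Table A2). Boost CTV = GTV, and CTV = GTV + 5 mm (Appendix 1.3.2). The same 2 or 3 mm PTV margin is added to each (Appendix 1.3.3).

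**Step 1: reproduce the protocol's own dose figures.** For total dose D in n fractions at alpha/beta 2, EQD2 = D x (D/n + 2)/4.

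- 4 x 7.5 Gy: 30 x 9.5/4 = 71.25 Gy (section 5.2 states 71).
- 4 x 5.5 Gy: 22 x 7.5/4 = 41.25 Gy (section 5.2 states 41).

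Both agree, so the same formula is used below.

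**Step 2: turn the limits into doses.**

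| Volume | Appendix 1.5 maximum | Table A2 maximum |
|---|---|---|
| Boost PTV (30 Gy) | 1.30 x 30 = 39.0 Gy | 1.07 x 30 = 32.1 Gy |
| Outer PTV (22 Gy) | 1.07 x 22 = 23.54 Gy | 1.30 x 22 = 28.6 Gy |

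The boost maxima differ by 39.0 − 32.1 = 6.9 Gy. In EQD2 terms:

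- 39.0 Gy in 4 (9.75 Gy per fraction): 39.0 x 11.75/4 = 114.6 Gy.
- 32.1 Gy in 4 (8.025 Gy per fraction): 32.1 x 10.025/4 = 80.5 Gy.

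**Step 3: can the outer limits be met?** Because both PTVs use the same set-up margin, the outer PTV contains the boost PTV.

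- *Appendix 1.5.* The enclosed boost is prescribed 30/22 = 136.4% of the outer prescription, against a cap of 107%. Even the 95% boost level, 0.95 x 30 = 28.5 Gy, exceeds the cap by 28.5 − 23.54 = 4.96 Gy. With no exclusion stated, no plan that delivers the boost can comply.
- *Table A2.* The outer limit excludes PTV36Gy, but the regimen has no 36 Gy volume. Taken literally, the 30 Gy boost stays inside a volume capped at 28.6 Gy. If the label means PTV30Gy (boost), the 28.6 Gy cap lies just above the 28.5 Gy boost level (28.5/22 = 129.5%). The margin is 0.1 Gy, so the limit is attainable, though narrowly.

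**Step 4: where do the two versions overlap for the boost?** A boost maximum at or below 107% (32.1 Gy) satisfies both boost limits. A maximum between 107% and 130% satisfies only Appendix 1.5.

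**The case against.** The best defence is that one of the conflicting statements is not what it seems. Three readings are possible.

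1. Appendix 1.5 has exchanged its two labels and Table A2 is right. The closeness of 28.6 Gy to 28.5 Gy supports this. So does section 5.2, which appears to make a similar PTV/PTVboost exchange when it discusses EQD2 levels.
2. The 107% sentence is left over from the 10 x 3.5 Gy arm. The Appendix is headed "Radiotherapy Treatment Protocol for arm 1" but still carries text for both arms: "The GTV is defined as the contrast enhancing lesion on CE-T1 MRI sequence for both treatment groups" and "The CTV of both, the experimental arm and the standard arm, is defined as the GTV".
3. A 130% boost hot spot is intended, and the boost cell of Table A2 is wrong.

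None of these removes the boost conflict. The 130% sentence is expressly about the boost of the experimental arm, and Table A2 caps that same volume at 107%.

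Other parts of the defence stand.

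- A reader might infer that neither outer limit can be met. For Table A2 that rests on a single subscript, which could be a slip for 30Gy. Read that way, the limit can be met.
- A reader might infer that Table A2 should simply be adopted. The first reading is the likelier, but it is not established. If the subscript is a genuine remnant of a 36 Gy boost, the matching level would be 0.95 x 36 = 34.2 Gy, and the fit to 28.6 Gy could be chance.
- A reader might infer that centres can diverge unnoticed while fully compliant. A centre that follows all of Appendix 1.5 meets an impossible outer cap, which is likely to prompt a query. Silent divergence is therefore less likely than the two boost figures alone suggest.

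**Conclusion.** The contradiction is in the text and needs no inference. The boost maximum is 130% in Appendix 1.5 and 107% in Table A2, that is 39.0 v 32.1 Gy (EQD2 about 115 v 80 Gy at the protocol's alpha/beta of 2), with no rule of precedence. The 23.5 Gy outer cap in Appendix 1.5 is unattainable as written. The 28.6 Gy outer cap in Table A2 is unclear only because of the undefined PTV36Gy.

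The scope is limited. Prescribed doses are stated consistently in section 3, section 5.2, Appendix 1.5 and Table A2. The organ-at-risk limits in Appendix 1.6 apply either way. Sample size and error rates do not change. The EQD2 figures describe permitted maxima and are not estimates of risk. Nothing in the protocol shows that any patient was treated differently, and no effect on the OS comparison is shown.

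It still needs correcting. A maximum-dose rule in the operative instructions for re-irradiation contradicts itself, and with it the standard for judging compliance.

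**What to change.** The sponsor's radiotherapy leads should confirm one set of maximum-dose limits for the boost PTV and the outer PTV. The Table A2 values are the likelier intention, but the decision is theirs. Then:

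1. State the same limits in Appendix 1.5 and Table A2.
2. Explicitly exclude the boost PTV from the outer PTV limit in both places.
3. Replace PTV36Gy in Table A2 with PTV30Gy (boost).
4. Notify the participating sites.

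The cost is one decision, text corrections in two places and a site memo. Sample size and analysis are unchanged.

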### 3. STUDY DESIGN

The original 2019 RISING-trial (RISING trial A) was designed as an open label, randomized, non-inferiority, phase III trial with 1:1 allocation for 130 patients. In this trial 13 patients were included in the experimental arm and 16 patients were included in the control arm. The updated 2023 RISinG trial (RISING trial B) is designed as a phase II, multi-center, clinical trial with a historic control group. The additional recruitment period of this phase will be approximately 30 months with an active follow-up time of 12 months.

The 13 patients of the RISING trial A will be supplemented until a total of 66 patients is reached. These patients fulfilling the inclusion criteria will get the following treatment:

- Hypofractionated radiotherapy with SIB in 2 weeks  
4 fractions of 7.5 Gy SIB to the GTV  
And 4 fractions of 5.5 Gy to the CTV (GTV + 5mm margin).

We will compare the survival of this group with a retrospective control group of patients, subtracted from the retro-RISinG registry study, a multi-center retrospective nation-wide population based cohort study, in which details of patient-, tumor- and treatment-related data of all patients with a recurrence of a primary brain tumor since January 2002 up to December 2022 in the Netherlands will be collected. We will select 99 matched patients in total with the following treatment:

- Moderately hypofractionated radiotherapy in 2-3 weeks  
10 fractions of 3.5 Gy to the CTV (GTV + 5 mm margin)

An overview of the target volume definitions and dose prescriptions is presented in table A3 in section 1.8 of the Appendix.

This control group will be matched to the patients in the experimental arm on an individual level for:

1. Age;
2. Gender;
3. WHO-grade primary tumor;
4. Time interval in between first radiation and re-irradiation;
5. MGMT-status.

[figure not shown]

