### 5.2 Experimental treatment arm (arm 1)

Since prospective phase III research on the optimal fractionation regimen is sparse, a radiobiological theoretical optimal regimen is chosen from retrospective studies and phase I/II studies. The linear-quadratic model describes cell killing, both for tumor control and for normal tissue complications following exposure to a varying amount of radiation. The most modern method of comparing fractionation schedules is to use the linear quadratic equation to calculate the equivalent dose in 2 Gy fractions (EQD2). For  $PTV_{boost}$ , the EQD2 may be up to 40 Gy based on the maximal cumulative dose of 100 Gy advised by Sminia and Mayer [32, 33]. For this reason, the dose on PTV was selected to be 4 fractions of 5.5 Gy ( $EQD2_{\alpha/\beta=2} = 41$  Gy).

For PTV, the maximal dose should not exceed 8 fractions of 5 Gy ( $EQD2_{\alpha/\beta=2} = 70$  Gy). In a prospective phase I trial, hypofractionated stereotactic radiotherapy was given using 5 Gy per fraction to doses ranging from 20 to 50 Gy on a dose escalation program, in patients with recurrent glioma with a median target volume of 24cc. Exceeding 8 fractions of 5 Gy resulted in 6.4 times more radiation damage [26]. Four fractions of 7.5 were considered safe with a comparable  $EQD2_{\alpha/\beta=2}$  of 71 Gy.

Experimental treatment schedule will be 4 fractions of 7.5 Gy SIB to the CE on CE-T1 and 4 fractions of 5.5 Gy to the CE with a 10mm margin.

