##### 1.3.3 Planning Target Volume (PTV)

The PTV and PTVboost are defined as the CTV and stereotactic CTVboost plus an isotropic 2 or 3 mm margin depending on radiotherapy center, to account for day to day setup variation related to the ability to immobilize the participant. The PTV should not extend outside the body contour.

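### Appendix 1.5 and Table A2 exchange the maximum-dose limits for the boost and the PTV in arm 1, neither is said to govern, and the 107% PTV limit in 1.5 cannot be met as written

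*Protocol*

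**What the plan says.** Protocol section 5.1 makes the whole of Appendix 1 the planning instruction: "Radiotherapy will be planned and delivered in every center according to the treatment protocol (Appendix 1". Section 3 also sends the reader to the overview table: "An overview of the target volume definitions and dose prescriptions is presented in table A3 in section 1.8 of the Appendix". The table in Appendix 1.8 is in fact headed A2.

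Appendix 1.5 prescribes 4 fractions of 5.5 Gy to the PTV and 4 fractions of 7.5 Gy to PTVboost. Its ceiling for the boost, followed by its ceiling for the PTV, reads: "should not exceed 130% of the prescription dose. Maximum dose in the PTV should not exceed 107% of the prescription dose". It gives no volume over which the maximum is read, and it does not take the boost out of the PTV.

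Table A2 accepts 95% to 107% for PTV30Gy (boost). For PTV22Gy it accepts "95% - 130% (exclude PTV", with the excluded volume labelled 36 Gy. Both rows specify Dmax 0.1cc. No volume with a 36 Gy label is defined anywhere in the protocol.

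On geometry, Appendix 1.3.2 sets the boost CTV equal to the GTV and forms the CTV from the GTV "with addition of a 3-dimensional margin of 5 mm limited by anatomic borders". Appendix 1.3.3 turns both into planning volumes in the same way, "plus an isotropic 2 or 3 mm margin depending on radiotherapy center". Section 5.2 gives a different CTV margin: "4 fractions of 5.5 Gy to the CE with a 10mm margin".

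**The concern.** Two current parts of one binding treatment instruction give exchanged dose ceilings, and nothing ranks them. A centre working from 1.5 may accept a boost maximum that a centre working from Table A2 must reject. The PTV ceiling in 1.5 also looks incompatible with the boost that the same paragraph prescribes.

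Three things are at stake.

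- **Dose to brain.** Appendix 1.3.4 names uninvolved brain as an organ at risk, but the constraint table in Appendix 1.6 sets no limit for it. Apart from the brain stem, the target maxima are the only numeric limits in Appendix 1 on dose to brain in and around the target. Necrosis is one of the toxicities reviewed at the interim looks (section 8.3).
- **Safety rationale.** Section 5.2 argues from the prescribed boost dose: "Four fractions of 7.5 were considered safe with a comparable" EQD2 of 71 Gy. It does not discuss the maximum above prescription that either ceiling allows.
- **Compliance.** The per-protocol analysis of overall survival (section 8.1.1) requires that there be no major violations. Dose compliance cannot be judged consistently against two opposite limits.

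**Working it through.** **Inputs.** Prescriptions: PTV 4 × 5.5 = 22 Gy and PTVboost 4 × 7.5 = 30 Gy (Appendix 1.5). Percentage limits: Appendix 1.5 and Table A2. Margins: Appendix 1.3.2 and 1.3.3, and section 5.2. α/β = 2 (sections 5.2 and 5.3).

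**Reproducing the protocol's own figures.** EQD2 = n·d·(d + 2)/(2 + 2).

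- 4 × 5.5 Gy: 22 × 7.5/4 = 41.25 (protocol: 41)
- 4 × 7.5 Gy: 30 × 9.5/4 = 71.25 (protocol: 71)
- 8 × 5 Gy: 40 × 7/4 = 70.0 (protocol: 70)
- 10 × 3.5 Gy: 35 × 5.5/4 = 48.1 (protocol: 48)

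The protocol's calculations are correct. The fault is an inconsistency between two texts.

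**Permitted maxima.** With four fractions, a total dose D has EQD2 = D·(D/4 + 2)/4.

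| Volume | Appendix 1.5 | Table A2 |
|---|---|---|
| Boost (30 Gy) | 1.30 × 30 = 39.0 Gy; EQD2 39.0 × 11.75/4 = 114.6 | 1.07 × 30 = 32.1 Gy; EQD2 32.1 × 10.025/4 = 80.5 |
| PTV (22 Gy) | 1.07 × 22 = 23.54 Gy | 1.30 × 22 = 28.6 Gy |

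The boost ceilings differ by 39.0 − 32.1 = 6.9 Gy, or 114.56 − 80.45 = 34.1 Gy in EQD2.

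**Does the boost lie inside the PTV?** PTVboost is GTV + 2 or 3 mm. PTV is GTV + 5 mm + 2 or 3 mm, that is 7 or 8 mm. With the 10 mm margin of section 5.2 it is 12 or 13 mm. Either way the PTV contains the boost. An anatomic border narrows the rim between the two but does not put the boost outside.

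**Can the 1.5 PTV limit be met?** The boost prescription is 30/22 = 136.4% of the PTV prescription, which is 30 − 23.54 = 6.46 Gy above the cap. Even the 95% boost minimum in Table A2, 0.95 × 30 = 28.5 Gy, is 28.5/22 = 129.5%. As written, the limit cannot be met by any plan that delivers the boost.

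**If 1.5 is read as leaving the boost out.** Dose would have to fall from at least 28.5 Gy at the boost edge to at most 23.54 Gy just outside it, a drop of 4.96 Gy. Under Table A2 the ceiling just outside is 28.6 Gy, which accommodates the 28.5 Gy boost minimum with 0.1 Gy to spare.

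**The case against.** The strongest reply is that the boost limits are both upper bounds. A plan that keeps the boost at or below 107% satisfies both, so a cautious centre can comply today. Only plans between 32.1 and 39.0 Gy are in dispute. The hard limits for optic nerves, chiasm and brain stem hold under either text. This stands and limits the size of the point, but 1.5 still permits what Table A2 forbids.

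It can also be said that 1.5 obviously did not mean its PTV cap to cover the boost, since one paragraph prescribes both doses. That is a fair reading of intent. The text nevertheless lacks the exclusion, and adding it still leaves 107% in 1.5 against 130% in Table A2.

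The metrics differ too. Table A2 reads Dmax over 0.1cc; 1.5 names no volume. If 1.5 means the hottest point, a 39.0 Gy limit on that point allows a Dmax 0.1cc of at most 39.0 Gy, so the gap on Table A2's metric is at most 6.9 Gy. The figure should be taken as nominal.

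Two further objections have weight. Which dose deviations count as major may be settled in a statistical analysis plan that is not at hand, so the per-protocol consequence is a risk only. And the interim rule in section 8.3 acts on tumour size, not on dose limits.

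A reader might infer that Table A2 settles the matter. It is the more coherent text for the PTV, but it excludes a volume that does not exist, and both 107% and 130% for the boost can be planned alongside a 130% PTV limit. The intended boost maximum cannot be read off the document. Nor does section 5.2 decide it: the EQD2 of about 70 Gy there describes a prescription, and even the 107% maximum gives 80.5 Gy.

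**Conclusion.** The instruction is wrong as written: two current sections give exchanged limits without an order of precedence, and one of the four limits cannot be met literally. The nominal size is a boost maximum of 39.0 versus 32.1 Gy (EQD2 114.6 versus 80.5 Gy) and a PTV maximum of 23.54 versus 28.6 Gy. The EQD2 figures assume α/β = 2 and four equal fractions, as the protocol does.

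A reader might go on to infer that centres have treated patients to different maxima, or that the trial's conclusion is affected. The document supports neither. These are permitted maxima, no delivered plan is shown to differ, and the sample size and primary test do not depend on them. The point should be corrected because it concerns dose limits for patients in treatment and is cheap to put right.

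**What to change.** 1. The sponsor's radiotherapy lead confirms the boost limit and the PTV limit together. One set then goes into both Appendix 1.5 and Table A2, on the same metric (Dmax 0.1cc).
2. State the PTV limit for the PTV outside PTVboost. Table A2's 130% (28.6 Gy) is the likely intended value, because it just accommodates the 28.5 Gy boost minimum. It still needs confirming, since the geometry shows only that the boost must be excluded.
3. In Table A2, change the excluded volume from PTV36Gy to PTV30Gy (boost).
4. Until confirmation, plan the boost to at most 107% (32.1 Gy), because that meets both stated boost limits. If 130% (39.0 Gy) is confirmed, add its justification to section 5.2.

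The cost is one confirmation and one short amendment. Prescription, endpoint, sample size and analysis stay as they are.

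Two clerical slips are separate and can go into the same amendment: section 5.2 exchanges the PTV and PTVboost labels on its 40 and 70 Gy figures, and section 3 should cite Table A2, not A3. The 5 mm versus 10 mm CTV margin is a separate inconsistency that does not alter this point.

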### 1.6 Dose Limitation to Organs at Risk

It is important to minimize the dose to the OARs whenever possible. This must be weighed against the possibility of sub-optimal treatment of the target volume.

**Table A1. Dose constraints for OARs in Gy. Radiobiological calculations performed with  $\alpha/\beta = 2$  Gy. To calculate the dose constraint at ReRT, the initial dose should be subtracted from the cumulative dose constraint for OARs. Subsequently, the ReRT EQD2 should be converted to the dose constraint for the OARs according to the treatment arm. The ReRT dose of OARs should never exceed the EQD2 and total dose constraint given for initial treatment (shown in column 'Constraint at ReRT').**

*Example:* Optic Chiasm ReRT dose = 9.8Gy ( $\leq 38$ ) in 10 fractions = 7Gy EQD2 ( $\leq 54$ ). Initial dose 53.2Gy in 30 fractions = 51Gy EQD2. Cumulative dose = 51 + 7 = 58Gy, is  $\leq 81$ .

| Constraint | OAR             | Constraint at ReRT (without considering previous radiation therapy)                |                                                              | Cumulative constraint
(Initial RT + ReRT)                  |
|------------|-----------------|------------------------------------------------------------------------------------|--------------------------------------------------------------|---------------------------------------------------------------|
|            |                 | Total D max 0.1cc dose (unless otherwise specified) at $\alpha/\beta=2$ |                                                              |                                                               |
|            |                 | EQD2                                                                               | Total physical dose at
4 x 7.5 Gy and 4 x 5.5 Gy          | EQD2                                                          |
| Hard       | Optic nerves    | $\leq 60$ Gy                                                                       | $\leq 27$ Gy                                                 | $\leq 90$ Gy                                                  |
|            | Optic chiasm    | $\leq 60$ Gy                                                                       | $\leq 27$ Gy                                                 | $\leq 90$ Gy                                                  |
|            | Brain stem      | $\leq 60$ Gy                                                                       | $\leq 27$ Gy                                                 | $\leq 90$ Gy                                                  |
| Soft       | Optic nerves    | $\leq 55$ Gy                                                                       | $\leq 26$ Gy                                                 | $\leq 83$ Gy                                                  |
|            | Optic chiasm    | $\leq 55$ Gy                                                                       | $\leq 26$ Gy                                                 | $\leq 83$ Gy                                                  |
|            | Brain stem      | $\leq 55$ Gy OR
54-59 Gy < 10cc                                                 | $\leq 26$ Gy OR
26-27 Gy < 10cc                           | $\leq 83$ Gy OR
81-89 Gy < 10 cc                           |
|            | Eye balls       | $\leq 45$                                                                          | $\leq 23$ Gy                                                 | $\leq 68$ Gy                                                  |
|            | Lenses          | D Mean $\leq 6$ Gy
D max 10 Gy                            | D Mean $\leq 6$ Gy
D max 0.1cc 9 Gy | D Mean $\leq 9$ Gy
D max 0.1cc 15 Gy |
|            | Pituitary Gland | D Mean $\leq 45$ Gy                                                     | D Mean $\leq 23$ Gy                               | D Mean $\leq 68$ Gy                                |
|            | Cochlea         | D Mean $\leq 45$ Gy                                                     | D Mean $\leq 23$ Gy                               | D Mean $\leq 68$ Gy                                |

